## Abstract

**Background:**

Spinal manipulation is the primary therapy utilised by chiropractors in the management of their patients. The skills required may feel foreign to chiropractic students as they need strength and endurance in movement patterns they may not have otherwise been exposed to. This may lead to injury while learning manipulative techniques. It is plausible to suggest that the implementation of a strength and conditioning program early in a practitioner’s career could reduce the incidence and progression of injuries. The study aims to test the effectiveness of a strength and conditioning program in reducing the risk of chiropractic students’ acquiring injuries while learning the skill of spinal manipulation.

**Methods:**

This study will involve a prospective cohort of chiropractic students who are currently learning manual therapy at an undergraduate level. Participants will be eligible for inclusion if they are enrolled in 3rd or 4th-year chiropractic manual therapy units at Murdoch University chiropractic course. The intervention group will follow a 12-week strength and conditioning program comprised of preventative exercises that address each body region previously identified as being prone to injury. The control group will complete a 12-week walking program. The primary outcome is injury rate, measured via a short questionnaire. The secondary outcome will be strength, measured via submaximal strength tests.

**Discussion:**

The prescribed exercises are aimed at improving the strength and endurance of those muscle groups involved in commonly taught manual therapy tasks. The resistance bands have been chosen as they are inexpensive, simple to implement for the purposes of the study, and acceptably safe. A video format was selected to allow ease of access for participants, provide a detailed description and a visual representation of the exercises to be performed. A questionnaire was designed as a means to assess the influence of the strength and conditioning program on injury rate and the impact this may have on the students’ ability to continue practicing. The International Physical Activity Questionnaire has been chosen to measure the participants level of activity before beginning the exercise program.

**Conclusion:**

This research protocol will be the first large-scale study to investigate the effectiveness of a strength and conditioning program to reduce injuries within chiropractic students learning manual therapy.

**Trial registration:**

Australia New Zealand Clinical Trials Registry (ACTRN12617001638325p).

**Electronic supplementary material:**

The online version of this article (10.1186/s12998-018-0192-0) contains supplementary material, which is available to authorized users.

## Background

Spinal manipulation is the primary therapy utilised by chiropractors in the management of their patients [1]. The skill required to deliver an effective manipulation takes several years of training at a tertiary institute. The motor control and movement patterns required may feel foreign to students, leading to imperfect technique and sometimes injury [2]. Among student and early career chiropractors, injury rate has been shown to range from 31 to 56% [1–5]. A retrospective survey of students from the Canadian Memorial Chiropractic College (CMCC) revealed that reports of adverse reactions were highest in the second year of the course when many techniques were initially taught [4].

The most injured body regions seem to vary within the literature, but common areas include the shoulders, wrists, neck and the lower back [3]. Of these, the most common forms of injuries were ligament sprain, tendonitis and muscular strain. It is important to note that some studies did not separate those injuries that occurred while delivering a technique and those that happened while receiving it. However, because chiropractors appear at risk of injury within their first five years of practice, rather than only during their education, delivering a manipulation is likely to be at least part of the reason for becoming injured [3].

Literature suggests that different population subsets had a greater risk of developing complications in specific areas. Females were found to have an increased risk of lower back, wrist and shoulder injuries, while males were more likely to develop injuries to the neck [2]. Almeida et al. [6] suggested that females report training injuries more frequently than males, but they comment that this could be attributable to disparities in symptom reporting rather than a true difference in injury rate.

There is currently conflicting evidence as to whether a higher body mass index (BMI) increases the risk of developing an injury during manual therapy training within a chiropractic program. Ndetan et al. [5] established that students who were overweight or obese were more likely to report an injury affecting the lower back while receiving a manipulation and a neck or shoulder injury while delivering one. However, Holm and Rose [3] suggest there is no association between, age, height, or weight and developing an injury while learning manual therapy skills. They proposed that it is physical capabilities rather than body measurements that contribute to training-related injuries in student chiropractors.

The high injury rate in the first five years of practice suggests that new chiropractors may not have the necessary strength and conditioning or use less than optimal biomechanics when manipulating [3]. It appears likely that those chiropractors in the early stages of their career begin to modify their technique to reduce mechanical stress on their bodies. Holm and Rose [3] suggest that optimal biomechanical positions should be promoted with students on an individual basis.

Manipulative techniques taught within chiropractic colleges often require awkward postures such as bending, stooping and rotating while simultaneously applying forces [2]. Chiropractors are subjected to these dynamic motions on a regular basis, which may result in undesirable biomechanical loading and subsequent injury [7]. This may be additionally true for chiropractic students due to their inexperience and increased time under load while they refine their technique including positioning, anatomical contacts, and delivery of the manipulative force.

In addition to this, Stock [8] identified a causal relationship between musculoskeletal conditions of the hand and wrist with repetitive forceful work. A more recent study suggested that force is the primary ergonomic risk factor for hand disorders amongst manual workers, though repetition may play a role. These findings may have implications for those who undertake repetitive forceful manipulations. Interestingly, there is little evidence to suggest that working with the hand in a non-neutral position is a risk factor for wrist and hand injury [9].

Injuries to chiropractic students and chiropractors early in their professional careers could have a significant effect on their longevity in the profession and affect their personal life. Depending on the severity and chronicity of an injury, ramifications could include; adverse impact on skills mastery, earning potential, quality of life, and even impact psychological well-being. Therefore, it is in the best interest of both students, educational and accrediting bodies to reduce the risk of personal injury to chiropractic students and chiropractors.

Our literature search failed to reveal any strength and conditioning program for chiropractic students to prevent injury while learning manipulative techniques or in the first years of practice. The concept of a strength and conditioning plan with the aim of reducing the likelihood of injury is worth considering as the implementation of such a program early in a practitioner’s training and career could reduce the incidence and progression of injuries. Similarly, Bork et al. [10] suggested that “specific strategies should be developed to reduce work-related musculoskeletal disorders in the practice of physical therapists”. In the 15 years since that study was published, researchers are yet to explore avenues to reduce the prevalence of injuries amongst manual therapists in training. The purpose of this research protocol is to develop a plan for a large-scale study to examine the effectiveness of a strength and conditioning program to prevent injuries related to manual therapy training and practice.

## Methods

### Study design

A randomised controlled trial of chiropractic students at Murdoch University using a preventative strength and conditioning program to prevent injury. This randomised controlled trial protocol complies with the recommendations of the SPIRIT guidelines [11].

### Participants

#### Study setting

This study will take place at Murdoch University, within the School of Health Professions.

#### Recruitment

Participants will be recruited from the 3rd and 4th year Chiropractic Science cohort at Murdoch University when manual therapy training is at its most intense. Students will be informed of the study and recruited through word of mouth, direct email and student Facebook groups.

#### Inclusion criteria

Potential participants will be either female or male students 18 years or older studying chiropractic on either a full or part-time basis.

#### Exclusion criteria

Potential participants will be excluded from this study if they are currently suffering from musculoskeletal pain in the shoulder, neck or low back region or have done so in the past 3 months or have a reported chronic physical disability.

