#### Feasibility study

We conducted an initial feasibility study around the design of region-specific exercises that hypothetically strengthen and improve the endurance of the at-risk anatomical areas of the shoulder, wrist and low back described above. Video clips and written instructions for each exercise of the protocol were developed and are described below. These will be supplied to the participants.

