### Outcomes

#### Primary outcome

##### Injury rate

Measured via a brief questionnaire designed especially for this study, which asks about shoulder, wrist or low back pain. It will ask for information about the pain frequency, duration, intensity, if the pain began while practising their manual therapy skills, and if they were in the role of ‘doctor’ or ‘patient’ at the time. Self-reported region specific numerical rating scales are included to measure pain intensity [29]. The questionnaire will ask if this has impacted their ability to continue to practice their skills or their Activities of Daily Living (ADLs). It will be administered at the beginning and every 4 weeks during the trial, i.e. 3 times over 12 weeks. The questionnaire will be completed online at weeks 4 and 8, with SMS reminders sent to participants in these weeks.

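### The entry screen (shoulder, neck, low back) does not match the primary outcome regions (shoulder, wrist, low back), so wrist pain present at entry could be counted as an injury and dilute the effect

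*Protocol article*

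**What the plan says.** All places are in the protocol article.

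- **Exclusion criteria.** A student is excluded if "currently suffering from musculoskeletal pain in the shoulder, neck or low back region or have done so in the past 3 months", or if they "have a reported chronic physical disability". The wrist is not listed.
- **Outcomes, Injury rate.** The primary outcome is measured by a purpose-made questionnaire "which asks about shoulder, wrist or low back pain". The neck is not listed. The questionnaire also covers how long the pain has lasted and "if the pain began while practising their manual therapy skills". On timing: "It will be administered at the beginning and every 4 weeks during the trial".
- **Background.** The "common areas include the shoulders, wrists, neck and the lower back".
- **Feasibility study and exercise sections A to C.** The exercises were designed for the "at-risk anatomical areas of the shoulder, wrist and low back described above". No neck exercise is described.
- **Abstract, Methods.** The programme is said to consist of "preventative exercises that address each body region previously identified as being prone to injury".
- **Baseline measures** records earlier related injuries and repeats a questionnaire every 4 weeks to follow injury status. **Statistical analysis plan** compares changes in injury rates after adjustment for baseline measures, without saying which ones.

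**The concern.** In a prevention trial, an exclusion for current or recent pain normally serves to ensure that participants start free of the condition that will later be counted. Here it does so for two of the three outcome regions. For the wrist it does not, although the Background lists the wrist among the common sites and recruitment targets the years when manual training is heaviest. If wrist pain that predates randomisation is scored as an injury, it adds events that the programme had no chance to prevent. Both arms' rates then rise and the contrast shrinks.

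The neck is the reverse case. Students with neck pain are kept out, but neck pain is neither an outcome nor a target of the exercises. The purpose of that exclusion is then unexplained, and a conclusion about injury in general would cover a site that the primary outcome does not observe.

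**Working it through.** **1. The region lists side by side**

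| Region | Background: common site | Screened at entry | Exercised | In primary outcome |
|---|---|---|---|---|
| Shoulder | yes | yes | yes | yes |
| Wrist | yes | **no** | yes | **yes** |
| Low back | yes | yes | yes | yes |
| Neck | yes | **yes** | no | **no** |

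The screen and the outcome disagree in two of the four rows.

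**2. Is existing wrist pain removed anywhere else?**

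- The chronic-disability exclusion may catch some long-standing cases, but not ordinary wrist pain.
- The onset item asks whether pain began during skills practice. Wrist pain that began in practice before enrolment would satisfy it.
- The duration item and the baseline administration could identify existing pain, but no rule says that they decide what counts as an event.
- Adjustment for unnamed baseline measures may recover precision. It does not reclassify an existing case as a non-event.

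The article therefore allows existing wrist pain to be counted. It does not say that it will be.

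**3. The plan's own sample size**

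The Sample size section gives 30% against 15%, alpha 0.05, 80% power and 106 per group, without stating sidedness. Two-sided formulas give 121 (pooled), 134 (with continuity correction), 118 (unpooled) and 119 (arcsine). One-sided pooled gives 95, or 108 with continuity correction; 95/0.90 = 105.6 would round up to 106 with a 10% dropout allowance. So 106 is matched only on one-sided readings that the article does not state. That is a separate matter. It is mentioned because the two-sided reference power used below is 74.7%, not 80%.

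**4. Worst-case dilution**

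Let w be the share of each arm that enters with wrist pain (assumed, since the documents give no figure). Suppose every such student is scored as an event whatever the arm:

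p′ = w + (1 − w)p, with p = 0.30 (control) and 0.15 (intervention).

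Power = Φ{ [d√n − 1.96√(2p̄(1 − p̄))] / √(p₁(1 − p₁) + p₂(1 − p₂)) }, with n = 106, d = p₁ − p₂, and p̄ the mean of p₁ and p₂.

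Reference, w = 0: d√n = 0.15 × 10.296 = 1.544; 1.96 × √0.34875 = 1.157; denominator √0.3375 = 0.581; Φ(0.387/0.581) = Φ(0.666) = 74.7%.

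Example, w = 0.05: control 0.05 + 0.95 × 0.30 = 0.335; intervention 0.05 + 0.95 × 0.15 = 0.1925; d√n = 0.1425 × 10.296 = 1.467; 1.96 × √0.38837 = 1.221; denominator √0.37822 = 0.615; Φ(0.246/0.615) = Φ(0.400) = 65.5%.

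| w (assumed) | Control | Intervention | Relative reduction | Power, two-sided, 106 per group |
|---|---|---|---|---|
| 0 | 30.0% | 15.0% | 50.0% | 74.7% |
| 2% | 31.4% | 16.7% | 46.8% | 71.0% |
| 5% | 33.5% | 19.25% | 42.5% | 65.5% |
| 10% | 37.0% | 23.5% | 36.5% | 57.2% |

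No figure is put on the neck: the article gives neither the share of injuries that affect the neck alone nor the regions covered by the 30% planning rate.

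**The case against.** A reader might infer that a student with wrist pain at entry will be scored as injured at week 4. The article does not say so. The baseline administration, the onset and duration items, the stated interest in changes of injury status and the adjustment for baseline measures all lean towards new or changed injury. A detailed event-coding rule may also sit in a fuller document that is not shown. This part of the objection stands, and it limits the point to what could be counted. It does not remove the point, because the two region lists are both printed and they differ.

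A reader might also infer bias between the arms. That does not follow: existing wrist pain is balanced by randomisation on average, and the expected result is a smaller observed effect.

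The power losses could be taken as the actual cost of the mismatch. They are an upper limit for each assumed w. They ignore the items that could identify existing pain, and they assume that the five wrist exercises leave that pain unchanged. The students concerned have also been screened free of shoulder, neck and low back pain for 3 months, so the true share with wrist pain may be at the low end. The gap between the stated 80% and 74.7% is not caused by this mismatch.

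On the neck, an outcome matched to the trained regions is coherent: the feasibility work, the exercises and the questionnaire all use the same three. The Background itself notes that the most injured regions differ between studies. Excluding students with neck pain narrows the population without distorting the comparison. One might go further and say that the outcome misses neck harm caused by the exercises, but nothing in the article documents such a risk. What stands for the neck is an unexplained exclusion, an inaccurate phrase in the abstract and an outcome label wider than what is measured.

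**Conclusion.** The mismatch is real and should be fixed. Wrist pain present at entry neither excludes a student nor is kept out of the primary outcome by any stated rule, so it could count as an injury in either arm. The consequence is misclassification and dilution towards no effect, not bias between arms.

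Its size cannot be known from the documents. If 2% to 10% enter with wrist pain and all of it is counted, the planned 50% relative reduction would appear as 46.8% to 36.5%, and two-sided power at 106 per group would fall by about 4 to 18 percentage points from 74.7%. This rests on the assumed prevalence, on full counting, and on no effect of the programme on existing wrist pain. If the baseline questionnaire is used to set such cases aside, most of the loss disappears.

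The neck part is a matter of scope: as written, the primary outcome supports a conclusion about the shoulder, wrist and low back only.

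**What to change.** Reconcile Exclusion criteria with Injury rate in one of two ways:

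1. Add the wrist to the screened regions. The cost is one word and a few more screen failures.
2. Keep eligibility as it is and state that an event counts only in a region that was pain-free on the baseline questionnaire. The data are already collected, so the cost is one sentence in the outcome definition. A student with wrist pain at entry still contributes shoulder and low back events.

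For the neck, choose one:

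1. Add a neck item to the 4-weekly questionnaire and report it as a separate, named outcome. The cost is one item. This has to be settled before follow-up starts, because neck pain that is not asked about cannot be reliably recovered later.
2. Limit the abstract wording and the conclusion to shoulder, wrist and low back, and either explain the neck exclusion or bring it into line with that scope. This costs wording only.

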#### Sample size

Based on an approximate and conservative baseline injury rate of 30% (0.3) derived from a comprehensive review [1, 5], a sample size of *n* = 212 (*n* = 106 per group) will have 80% power to detect a decrease in injury rate of 50% to an injury rate of 15% (0.15) in the treatment group (alpha = 0.05, beta = 0.2).

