#### Allocation

Random allocation will be achieved using Research Randomizer [12]. The participants will be randomised into two, equal sized block groups. The sequence will be concealed in opaque envelopes until the interventions are assigned. A member of the research team will be responsible for enrolling participants and implementing the randomisation process. The participants will not be blinded. The assessors and data analysts will be blinded to which group the participants are allocated to.

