#### Statistical analysis plan

Descriptive statistics for demographic and outcome data will be based on frequency distributions for categorical data and means and standard deviations or medians, interquartile ranges, and ranges for continuous data, as appropriate. Univariate analysis for treatment group comparisons will include χ^2^ and Fisher exact tests for categorical comparisons, and t-tests or non-parametric Mann-Whitney *U or Wilcoxon signed rank* tests for continuous outcomes. After adjusting for baseline measures, changes in injury rates and muscle strength and endurance over the course of the study will be compared between groups using repeated measures ANOVA or linear mixed models, depending on the final dataset. Data will be analysed using IBM SPSS version 24.0 (Armonk, NY) and *p*-values < 0.05 will be considered statistically significant. The IPAQ results will be used as a covariate in the analysis.

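### The stated 80% power at 106 per group holds only under an undeclared one-sided test; read two-sided, the planned analysis has about 75% (chi-square) or 70% (Fisher exact)

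*Protocol article*

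**What the plan says.** The Sample size section takes a baseline injury rate of 30%, which it calls approximate and conservative. It states that a trial with 106 in each arm "will have 80% power to detect a decrease in injury rate of 50% to an injury rate of 15% (0.15) in the treatment group", with "alpha = 0.05, beta = 0.2". It gives no test, no sidedness and no allowance for losses.

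The Allocation section makes the split equal: "The participants will be randomised into two, equal sized block groups".

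In the Statistical analysis plan section, "Univariate analysis for treatment group comparisons will include" chi-square and Fisher exact tests for categorical data, without choosing between them. The same section plans repeated measures ANOVA or linear mixed models for changes in injury rates. For p, it says that "values < 0.05 will be considered statistically significant". No part of the article mentions a one-sided test.

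**The concern.** The power statement is the article's only justification for the size of the trial, and it concerns the primary outcome. The usual two-sided calculation with the article's own rates, alpha and beta asks for more than 106 per group, so the type II error of the analysis as written would be about 25 to 30% instead of 20%. A null result would then be credited with more power to detect a halving of injuries than the trial had.

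**Working it through.** **Inputs.** From the Sample size section: p1 = 0.30, p2 = 0.15, difference d = 0.15, alpha = 0.05, power 0.80, n = 106 per group. From the Allocation section: 1:1. From the Statistical analysis plan section: chi-square or Fisher exact, p < 0.05. Sidedness is not stated, so both versions are run.

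Mean rate: (0.30 + 0.15)/2 = 0.225. Null variance term: 2 × 0.225 × 0.775 = 0.34875, square root 0.5906. Alternative variance term: 0.30 × 0.70 + 0.15 × 0.85 = 0.3375, square root 0.5809.

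**Step 1. Which calculation gives the plan's 106?**

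Pooled formula: n = [z_α × 0.5906 + 0.8416 × 0.5809]² / 0.15².

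- Two-sided (z_α = 1.960): (1.1575 + 0.4889)² / 0.0225 = 120.5, so 121.
- One-sided (z_α = 1.645): (0.9714 + 0.4889)² / 0.0225 = 94.8, so 95.

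Continuity correction: n_c = (n/4) × [1 + √(1 + 4/(n·d))]².

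- Two-sided: (120.5/4) × [1 + √(1 + 4/18.07)]² = 133.5, so 134.
- One-sided: (94.8/4) × [1 + √(1 + 4/14.22)]² = 107.7, so 108.

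Unpooled formula, two-sided: (1.960 + 0.8416)² × 0.3375 / 0.0225 = 117.7, so 118.

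Fisher exact, by enumerating all outcomes of two binomial samples:

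- Two-sided: power 79.69% at 130 and 80.08% at 131, so 131.
- One-sided: power 79.65% at 105 and 80.07% at 106, so 106.

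| Method | Two-sided n per group | One-sided n per group |
|---|---|---|
| Pooled normal (chi-square) | 121 | 95 |
| Unpooled normal | 118 | 93 |
| Arcsine | 119 | 94 |
| Continuity-corrected | 134 | 108 |
| Fisher exact | 131 | **106** |

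The stated number is returned exactly by the one-sided Fisher exact test and closely by the one-sided continuity-corrected formula. No two-sided entry is nearer than 118.

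**Step 2. Power at 106 per group, two-sided alpha 0.05.**

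- Pooled normal: Φ[(0.15 × √106 − 1.1575)/0.5809] = Φ(0.666) = 74.7%.
- Unpooled normal: Φ[0.15/√(0.3375/106) − 1.960] = Φ(0.698) = 75.8%.
- Chi-square without correction, exact enumeration: 75.5%.
- Continuity-corrected: 69.1% (normal approximation), 69.6% (exact enumeration).
- Fisher exact, exact enumeration: 70.3%.

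**Step 3. How far the target moves.** Keeping 106 per group and the pooled two-sided formula, 80% power is reached at 30% versus 14.1%: [1.960 × √(2 × 0.2205 × 0.7795) + 0.8416 × √(0.2100 + 0.1211)]² / 0.159² = 105.5.

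**The case against.** The strongest reply is that the sample size may have been calculated correctly. The target is directional, a decrease in injury rate; no sidedness is given; and Fisher's exact test is one of the two tests the analysis section names. A one-sided 5% Fisher test makes 106 the smallest size that reaches 80%. This stands, and it rules out the stronger reading that a reader might infer, namely that 106 is a plain arithmetic mistake that matches no method. The documents do not support that reading. What the reply does not do is carry the 80% over to the planned analysis. One-sided testing is declared nowhere, an unqualified p < 0.05 is conventionally two-sided, and chi-square and ANOVA F tests are non-directional as normally reported.

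A second reply is that 106 might be 95 inflated for 10% loss, since 95/0.90 = 105.6. That is also one-sided, and the text attaches the 80% to the 212 themselves without mentioning a loss rate, so it cannot be assumed.

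A third reply is that the shortfall is modest and the 30% baseline is described as conservative. The Background section cites 31 to 56%. With a halving from about 33% (33% versus 16.5%), the two-sided pooled formula needs 106.2 per group, so a slightly higher baseline would restore about 80%. This is fair as to size, but the claim made is for 30% versus 15%.

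A reader might also infer that the absence of an allowance for losses is part of the error. It is not. A condensed article may leave that to the full protocol, and no loss rate is given.

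**Conclusion.** The stated 80% does not apply to the analysis as written, if that analysis is read in the conventional two-sided way. Power for 30% versus 15% with 106 analysed per group is then about 75% with chi-square and about 70% with Fisher exact, a shortfall of about 5 or 10 percentage points. The number is consistent with a one-sided 5% Fisher exact test that the article never declares. The defect is an unstated condition and a mismatch between the sample size and the analysis. The conclusion rests on the two-sided reading of p < 0.05, on a simple comparison of two proportions, and on 106 per group with complete data. Power for the repeated measures or mixed models that the article also lists was not assessed.

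As a side note, any loss lowers the power further. With losses of 5%, 10%, 15% or 20%, all assumed because the article gives no rate, the two-sided pooled power would be 72.5%, 70.2%, 67.7% or 65.0%.

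**What to change.** In the Sample size section, state the sidedness and the test, and make both agree with the Statistical analysis plan section. For a two-sided analysis, restate the figure along these lines: 106 analysed per group gives about 75% power (two-sided chi-square, alpha 0.05; about 70% with Fisher exact) to detect 30% versus 15%. If 80% is to be claimed two-sided, quote 121 analysed per group (242 in total) for chi-square, or about 131 (262 in total) for Fisher exact. If a one-sided test was intended, declare it in both sections.

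The cost is one corrected paragraph and a somewhat less favourable power figure. Restating the power needs no extra participants; claiming 80% two-sided would need 30 more in total for chi-square (242 − 212) or about 50 more for Fisher exact (262 − 212), before any losses.
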